### Interim analyses {21b}

No interim analyses will be conducted during this study.

### Methods for additional analyses (e.g., subgroup analyses) {20b}

To explore the synergetic effect of NIKA and EMDR therapy, a two-level analysis (only accounting for repeated measures over time, thus not considering nesting of families within therapists) will be conducted to compare dyads who have received both NIKA and EMDR, to dyads who have only received NIKA. We will compare changes in disrupted parenting behavior, sensitive parenting behavior, child PTSD symptoms, and behavioral and emotional problems from the pre-test to the second post-test between these two groups, see the “Sample size {14}” section for more details about the analysis.

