#### Synergetic effects of attachment-based intervention and individual trauma therapy for the victimized parent

Because of the complementary primary foci of NIKA and EMDR therapy, it would be valuable to explore the synergetic effects of these two interventions. While NIKA adopts a trauma-sensitive approach by explicitly linking parents’ past traumatic experiences to dysfunctions in their current parenting behavior, for parents who suffer from PTSD symptoms, their ongoing trauma symptomatology might still be an interfering factor in the relationship with their child. Individual trauma therapy focused on reducing their own PTSD symptoms might then be additionally needed in order to further improve the parent-child relationship. Hence, we hypothesize that if parents with clinical PTSD symptoms additionally receive EMDR therapy after NIKA, they would show an even greater decrease in disrupted parenting behavior and a greater increase in sensitive parenting behavior compared to parents with clinical PTSD symptoms who only receive NIKA. Considering the direct and indirect impact of parental PTSD symptoms and related psychopathology on the development of young children, this should also be reflected in a stronger decrease in PTSD symptoms and related psychopathology of the child. This assumption has not yet been empirically tested, but several studies did investigate whether parental traumatization hampers the effectiveness of attachment-based parenting interventions. Although one study did not confirm this hypothesis [51], three other studies did show that traumatized parents responded less well to these interventions [52–54]. These latter findings support the assumption that individual trauma therapy focused on the parent, in addition to an attachment-based intervention such as NIKA, would generate increased effects.

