### Criteria for discontinuing or modifying allocated interventions {11b}

In case a mother refuses NIKA or EMDR, or does not want to complete all treatment sessions, we still aim to complete the research assessments for the dyad.

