### Participant timeline {13}

The total study duration for each participating dyad is 13 weeks. After informed consent is obtained, the mother and child are asked to participate in the pre-test, during which the mother is asked to fill out several questionnaires and 10 min of parent-child interactions are videotaped. In addition, we ask a social worker in the domestic violence shelter to fill out a questionnaire about the child. Prior to the pre-test, the dyad is allocated to NIKA or the waitlist usual care group (the dyad will be notified about this directly after the pre-test). NIKA consists of one intake and four 1-h sessions, divided over 5 weeks. During this time, dyads in the waitlist group only receive CAU in the domestic violence shelter. In week 7, a post-test is conducted, which is similar to the pre-test. Phase 2 of the design starts in that same week. Mothers who report clinical PTSD symptoms at the post-test are allocated to EMDR or the waitlist usual care group. EMDR consists of one intake and a maximum of five 90-min sessions over the course of 5 weeks. Mothers in the waitlist group only receive CAU during this period. Mothers who do not report clinical PTSD symptoms in phase 2 are not included in the randomization. They will still be involved in the post-test of phase 2, to prevent dropout bias (i.e., by making sure the investment for this study will be the same for each participating dyad, it is not likely that dropout rates will differ for the conditions). In week 13, the post-test of phase 2 takes place for all dyads, which is similar to the previous assessments. All assessments take place in the domestic violence shelter or, in case the dyad’s treatment is continued through ambulatory care, at the dyad’s home. The assessments are conducted by two trained (assistant) researchers and take approximately 1 h each. See Fig. 3 for an overview of the timeline for each dyad.

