The estimated effect size of EMDR therapy on PTSD symptoms of the mother is based on a recent meta-analysis in which effect sizes of EMDR therapy were reported within a range of *g* = 0.67–1.18 [79]. Because the current implementation of EMDR therapy (focus on memories of traumatic events that are related to their PTSD symptoms and also hinder positive parent-child interactions) is different from previous studies, we decided to stay on the conservative side of this range by assuming an effect size of *d* = 0.60 for this study. We estimated three-level models accounting for repeated measures over time (level 1) and nesting of mothers (level 2) within the previous condition (NIKA versus waitlist) (level 3). We estimated approximately 50% variance to occur between subjects and 5% variance between previous conditions (NIKA versus waitlist). For a sample of *N* = 80, (*n* = 40 per group), two time points, and two-sided testing with a significance level of *α* = .05, we will have 75% power to detect effects of *d* = 0.60. With a sample of *N* = 150 in phase 1, this would imply that 53% of the mothers who are recruited for this study should report clinical trauma symptoms in order to be included in the randomization for phase 2. We made this estimation based on a recent report which revealed that all women in one of the participating domestic violence shelter locations experienced severe and chronic domestic violence and 75% of the women report traumas of their own childhood [80].

To explore the synergetic effect of NIKA and EMDR therapy, a two-level analysis (only accounting for repeated measures over time, thus not considering nesting of families within therapists), estimating 80% variance to occur between subjects, we will have 68% power to detect effects of *d* = 0.50.

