### Methods in analysis to handle protocol non-adherence and any statistical methods to handle missing data {20c}

We will conduct multilevel multiple imputation [81, 82] to be able to include all dyads, including families who dropped out throughout the project, in the analyses (intention to treat).

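### The NIKA+EMDR versus NIKA-only analysis does not limit the comparator to mothers with clinical PTSD symptoms randomised in phase 2, contrary to the rationale, intention to treat and the stated power, and it estimates an add-on effect rather than synergy

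*Protocol article*

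**What the plan says.** The section Methods for additional analyses {20b} gives the only analysis text for the combined-treatment hypothesis. A two-level model is used "to compare dyads who have received both NIKA and EMDR, to dyads who have only received NIKA", on change "from the pre-test to the second post-test between these two groups". It sets no PCL-5 threshold and does not mention allocation.

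Other sections bear on who belongs in the NIKA-only group:

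- The rationale on synergetic effects expects a greater improvement with NIKA plus EMDR "compared to parents with clinical PTSD symptoms who only receive NIKA". The Objectives {7} state the same hypothesis but do not repeat the PTSD restriction for the comparator.
- Participant timeline {13}: "Mothers who do not report clinical PTSD symptoms in phase 2 are not included in the randomization". These mothers are still assessed at post-test 2, so their data will exist.
- Criteria for discontinuing or modifying allocated interventions {11b} plans for refusal: "In case a mother refuses NIKA or EMDR, or does not want to complete all treatment sessions", the assessments are still sought.
- The section on non-adherence and missing data {20c} commits the analyses to intention to treat, with all dyads included.
- Sample size {14}, for this analysis: "estimating 80% variance to occur between subjects", "we will have 68% power to detect effects of *d* = 0.50". No group sizes are given.

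The aim is called synergetic in the rationale, objectives and analysis sections, whereas the Discussion speaks of additive effects.

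**The concern.** The second randomisation covers only mothers with a PCL-5 score of 31 or more at post-test 1. Every NIKA-arm mother below that score has received NIKA and not EMDR, so she fits the literal description of the comparator although no randomisation put her there. She differs from the EMDR group in PTSD status by definition. A mother allocated to EMDR who refuses it also fits the description. An analyst following the section as written could therefore replace a randomised comparison with one confounded by PTSD status and by acceptance of treatment.

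The protocol itself gives grounds to expect different change in the two kinds of mother. Its rationale cites three studies in which traumatised parents responded less well to attachment-based interventions, and one that did not find this. If the pattern holds here, the literal comparator would improve more than it should and hide part of any benefit of EMDR.

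A separate matter is the label. NIKA plus EMDR against NIKA shows what EMDR adds once NIKA has been given. The contrast would be positive even if EMDR worked equally well without NIKA, so a positive result would not by itself support the word synergy.

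**Working it through.** **Inputs from Sample size {14}.** Phase 1: 150 dyads, 75 per arm. Phase 2: 80 mothers, 40 per arm, that is 80/150 = 53% of those recruited. Two time points, two-sided alpha 0.05 (stated for phases 1 and 2, assumed for this analysis). Between-subject variance is 50% for the two primary calculations and 80% for this one.

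**Method.** Power for a two-group comparison of change, with d in total-SD units, from the noncentral t distribution. SD of change = √(2(1 − ICC)), where ICC is the between-subject share. Noncentrality = d / [SD × √(1/n1 + 1/n2)]. The small therapist or previous-condition level is ignored.

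**Check of the method on the other stated figures.**
- Phase 1: SD = √(2 × 0.5) = 1; 0.50/√(2/75) = 3.06; power 86.0% (stated 86%).
- Phase 2: SD = 1; 0.60/√(2/40) = 2.68; power 75.5% (stated 75%).

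**Group sizes under the two readings.** Assume that the 80 eligible mothers split evenly over the phase 1 arms.
- Eligible in the NIKA arm: 75 × 80/150 = 40, hence 20 allocated to EMDR and 20 to waitlist.
- Not randomised in phase 2: 75 − 40 = 35.
- Restricted reading: 20 v 20. Literal reading: 20 v (20 + 35) = 20 v 55, with 35/55 = 64% of the comparator never randomised.

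**Which reading gives the stated 68%?** SD = √(2 × 0.2) = 0.632.

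| Reading | Noncentrality | Power at d = 0.50 |
|---|---|---|
| 20 v 20 | 0.50/(0.632 × √(1/20 + 1/20)) = 2.50 | 68.3% |
| 20 v 55 | 0.50/(0.632 × √(1/20 + 1/55)) = 3.03 | 84.8% |

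The stated power matches the restricted comparison, not the comparison as the analysis section words it.

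**Bias under the literal reading.** Bias = 0.636 × the difference in mean change between mothers without and with clinical symptoms. The documents do not give this difference. For an assumed 0.2 SD it is 0.636 × 0.2 = 0.13 SD; for 0.5 SD it is 0.636 × 0.5 = 0.32 SD. The target effect is 0.50. The effect of refusers cannot be sized, because no refusal rate is given.

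**Baseline.** Change runs from the pre-test, before NIKA and before the second randomisation; the EMDR primary comparison starts at post-test 1. Between randomised groups, change before randomisation is balanced in expectation, so the pre-test start adds no bias but can cost precision. Under the literal groups it would also carry differential response to NIKA into the contrast.

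**A contrast that does address synergy.** This is the EMDR effect in the NIKA arm minus the EMDR effect in the phase 1 waitlist arm, with about 20 mothers in each of four cells. SE = SD × √(4/20). For a difference of 0.50 SD:
- 80% between-subject variance: SE = 0.632 × 0.447 = 0.283; power about 42%.
- 50%: SE = 0.447; power about 20%.

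**The case against.** The strongest reply is that the document already shows what was meant. The rationale restricts the comparator to parents with clinical PTSD symptoms, and the 68% is the power of 20 v 20. A reader might infer from the analysis section that the plan has decided to include never-randomised mothers. The documents do not support that: they contradict themselves, and the weight of the evidence favours the restricted comparison. This stands, and it makes the point one of reconciliation.

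A reader might also infer that the analysis is deliberately by treatment received. The article, however, uses the verb receive for allocated groups elsewhere, including in its primary hypotheses, and its intention-to-treat statement exempts no analysis. What remains is that the section can be read either way and that refusals are foreseen.

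Nor does the pre-test baseline bias a comparison of randomised groups. The window is stated openly and describes total change over the whole sequence, so changing it is a matter of efficiency.

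Finally, synergy may be only a loose word, since the contrast is spelled out. That is partly right: no interaction is hypothesised. The label would still invite a conclusion that the contrast cannot carry.

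The analysis is exploratory and serves secondary hypotheses, which limits the consequences. Leaving detail to a fuller document does not dispose of the point, because the article positively states the groups, the window and the label.

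**Conclusion.** The concern holds as an internal contradiction in a secondary, exploratory analysis. It should be fixed, but no primary conclusion depends on it. As worded, the comparator would be about 55 dyads, of whom about 35 (64%) were never randomised in phase 2, against the 20 that the rationale and the stated 68% power imply. The possible bias of 0.13 to 0.32 SD applies only if the literal wording is followed, and it rests on an assumed difference in change of 0.2 to 0.5 SD. The counts rest on 53% eligibility spread evenly over the phase 1 arms. Whichever group is used, NIKA plus EMDR against NIKA estimates the add-on effect of EMDR given NIKA and is not by itself evidence of synergy.

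**What to change.** Reword the analysis in {20b}, and the Objectives to match:

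1. Limit it to NIKA-arm mothers with a PCL-5 score of at least 31 at post-test 1 who were randomised in phase 2, and compare them as allocated, whether or not they accepted EMDR.
2. Take post-test 1 as baseline with the pre-test as an additional covariate, as a gain in precision.
3. State the group sizes behind the 68% (about 20 v 20).
4. Call the result the add-on effect of EMDR after NIKA, and use one term for it throughout.
5. Optionally, among all mothers randomised in phase 2, report the EMDR effect in each phase 1 arm and the difference between them with a confidence interval, and reserve the word synergy for that difference. With about 42% power for 0.5 SD at 80% between-subject variance (about 20% at 50%), it is for estimation only.

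The cost is wording. All the data are already planned, and the stated power does not fall, because it already corresponds to the restricted comparison.

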### Methods in analysis to handle protocol non-adherence and any statistical methods to handle missing data {20c}

We will conduct multilevel multiple imputation [81, 82] to be able to include all dyads, including families who dropped out throughout the project, in the analyses (intention to treat).

### Plans to give access to the full protocol, participant-level data, and statistical code {31c}

We will archive our syntaxes and data documentation in Dataverse, in accordance with the guidelines for the archiving of academic research for faculties of Behavioural and Social Sciences in the Netherlands. Because the participant-level data include special categories of personal data, these data cannot be made openly accessible. However, we will share parts of the processed data that contain no personal information upon request.

## Oversight and monitoring

### Composition of the coordinating center and trial steering committee {5d}

This multicenter trial is coordinated by the researchers from Leiden University. [name] is the principal investigator of this study. [name] coordinates recruitment and data collection and remains in close contact with the contact person of each participating domestic violence shelter (at least once per week) throughout the study. A small group of core researchers, based at Leiden University, meet on a weekly basis to monitor the trial. The full research team meets on a monthly basis for this purpose. The main funder of this trial (ZonMw) serves as the steering committee and monitors the project through yearly evaluation meetings and reports.

### Composition of the data monitoring committee, its role, and reporting structure {21a}

No formal data monitoring committee was established for this study. A data manager and privacy officer from the Faculty of Social and Behavioural Sciences at Leiden University have approved the data management plan for this study and are regularly consulted by the researchers.

### Adverse event reporting and harms {22}

The families who participate in this study will receive the care they need in the domestic violence shelters. EMDR and similar short-term, attachment-based interventions to NIKA have been used extensively in other research (for an overview of EMDR studies, see, e.g., [83]; for comparable attachment-based interventions to NIKA, see, e.g., [31, 33]). No negative consequences have been reported in these studies, so we expect this to be the same for our study. In addition, both interventions are already extensively used in Dutch practice. The measurement instruments (questionnaires and parent-child observations) that will be used in this study have also been used in previous studies. In case mothers and/or children experience distress during the research appointments or intervention sessions, the researchers or therapists will provide the needed attention.

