#### The importance of addressing parental PTSD symptoms

Adults who are victims of interparental violence are at an increased risk for developing PTSD [37, 38]. This risk is further exacerbated by the fact that many victimized adults have a history of chronic and interpersonal traumatization themselves, for instance resulting from experiences of childhood maltreatment [39, 40]. In line with the concept of relational PTSD, it might be expected that if parents show reduced PTSD symptoms, for example after receiving trauma therapy, this would lead to improved parent-child interactions, more security for the child, and therefore a reduction of PTSD symptoms in the child as well. Following this line of reasoning, it would be important that parents who suffer from PTSD symptoms and related psychopathology receive trauma therapy to reduce their own PTSD symptoms—among which those symptoms that interfere with the parent-child relationship.

For individual treatment of adult PTSD, meta-analytic evidence consistently demonstrates the effectiveness of EMDR therapy and trauma-focused cognitive behavior therapy (TF-CBT) [41–45], also for adults with PTSD resulting from childhood maltreatment [46]. Both interventions are therefore recommended in several Dutch and international guidelines [47–49]. Nevertheless, several arguments favor the use of EMDR therapy relative to TF-CBT in the specific context of this study. First, a recent economic analysis showed that EMDR therapy is the most cost-effective trauma intervention for adults [50]. In addition, in the expert meeting that was organized for our preliminary study, the large majority of experts considered EMDR therapy as the most appropriate therapy for victimized parents who have experienced interparental violence, because this is an efficient therapy that leads to PTSD symptom reductions in a short time frame [36]. To our knowledge, the effectiveness of EMDR therapy (or any other trauma therapy) for the specific group of victimized parents after interparental violence has not yet been empirically investigated. In the current study, we aim to fill this gap by evaluating whether EMDR therapy can be used to reduce PTSD symptoms in this population.

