Furthermore, several background variables are assessed in this study: demographic variables (e.g., age, gender, SES), parental psychopathology (assessed at all time points with the Brief Symptom Inventory (BSI)-18 [73]), the maltreatment history of the child (assessed with the Modified Maltreatment Classification System [MMCS] based on case file coding [74]), parental childhood trauma (assessed during pre-test with the Childhood Trauma Questionnaire Short Form; CTQ-SF; [75]), and received professional support (e.g., other types of therapy provided to the family during the study, assessed based on case file coding). In addition, we will document all relevant characteristics of the participating domestic violence shelters (e.g., type of care that is provided to the families) and therapists (e.g., work experience, treatment fidelity).

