## Data collection and management

### Plans for assessment and collection of outcomes {18a}

At all three time points, the mother-child dyad is invited for a 1-h research appointment. All research appointments are similar in structure and content. After a short explanation of the (assistant-)researcher, the mother is asked to fill out a general questionnaire (only during the pre-test), the BSI [73], and CATS [70]. Then, a 10-min free play observation is conducted and videotaped. During the first 5 min of this observation, the mother and child are instructed to play together without toys as they would normally do. Next, a set of toys is provided, and the mother and child are instructed to play with these toys as they would normally do. The set of toys consists of a too large variety of toys, including a hand puppet, a toy that can make much noise, and age-inappropriate toys. Also, ambiguous toys (such as a spider and a police car) are included. After 4 min, the mother is instructed to clean up the toys with her child. These elements were included to make the play session a bit more challenging and stressful for the mothers. After the observation task, the mother is asked to fill out the CTQ [75], LEC-5 [60], PCL-5 [60], and CBCL [72]. All questionnaires are filled out on a laptop using the survey platform Qualtrics, or, in case this has the mother’s preference, on paper. The researcher remains in the same room during the administration of the questionnaires, so that the mother can ask questions. Because some questionnaires may elicit negative emotions in the mothers, the researcher remains vigilant of any signs of distress in the mother while she is filling out the questionnaires. If this occurs, the researcher will comfort the mother and pause the research appointment as long as necessary. At the end of the research appointment, the researcher will point the mother towards the possibility to contact her social worker if she would like to talk about anything related to the questionnaires. Even though the child is present during the observation talk, whenever possible the child will not be in the same room while the mother fills out the questionnaires. In most domestic violence shelters, there is an internal child care facility where the child can stay during this time. If this is not an option, the second researcher who is present will watch the child in another room while the mother fills out the questionnaires.

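### The harms section relies on other studies having reported no harm and plans no by-arm count of worsening; BSI-18 and phase 1 PCL-5 go uncompared

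*Protocol article*

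**What the plan says.** Protocol article, Adverse event reporting and harms {22}: the section notes that EMDR, and interventions similar to NIKA, have been studied widely, and continues: "No negative consequences have been reported in these studies, so we expect this to be the same for our study". It adds that both interventions are in extensive use in Dutch practice and that the instruments have been used before. The only action named is this: "In case mothers and/or children experience distress during the research appointments or intervention sessions, the researchers or therapists will provide the needed attention". The section does not say what is recorded, by whom, or how the arms would be compared.

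Oversight: "No formal data monitoring committee was established for this study", and Interim analyses {21b} states that there are none.

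Planned by-arm comparisons (Outcomes {12}):
- disrupted and sensitive parenting, NIKA versus waitlist, pre-test to first post-test;
- child CATS and CBCL/TRF, NIKA versus waitlist, over the same interval;
- maternal PCL-5, EMDR versus waitlist, first to second post-test.

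The additional analysis {20b} compares NIKA plus EMDR with NIKA alone on parenting and child outcomes. It uses neither PCL-5 nor BSI-18.

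Data collected: BSI-18 is listed among the background variables, as "parental psychopathology (assessed at all time points with the Brief Symptom Inventory (BSI)-18". On PCL-5, Plans for assessment {18a} says "All research appointments are similar in structure and content" and, of each appointment, "After the observation task, the mother is asked to fill out the CTQ [75], LEC-5 [60], PCL-5 [60], and CBCL [72". Participant timeline {13} has all dyads attend the second post-test, whether or not they were randomised in phase 2.

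**The concern.** The section that should say how harms are found and reported gives a reason for expecting none. For NIKA the reason is indirect, because the studies cited are of comparable interventions. Followed as written, the trial would report mean changes and would have no prespecified way of saying whether more mothers or children deteriorated in one arm than in the other.

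That matters here because a favourable mean can coexist with deterioration in a minority, and the article itself describes these families as extremely vulnerable. A later statement that no harms occurred would reflect partly that none were systematically counted. Much of the data needed is already being collected and has no planned use for this purpose.

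**Working it through.** **1. Arm sizes, checked against the article's own power figures (Sample size {14}).** For two means with a standardised difference d and n per arm, power ≈ Φ(d·√(n/2) − 1.960).
- Phase 1: n = 75, d = 0.50. 0.50 × √37.5 = 3.062 and Φ(1.102) = 0.865. The noncentral t gives 0.860. Stated: 86%.
- Phase 2: n = 40, d = 0.60. 0.60 × √20 = 2.683 and Φ(0.723) = 0.765. The noncentral t gives 0.755. Stated: 75%.

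This is the simple two-group formula; the three-level simulation was not repeated. It supports using 75 and 40 per arm below.

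**2. What the planned analyses cover.**

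| Measure | Phase 1, NIKA v waitlist | Phase 2, EMDR v waitlist | Individual worsening |
|---|---|---|---|
| Parenting | mean change | only NIKA+EMDR v NIKA, from pre-test | none |
| Child CATS, CBCL/TRF | mean change | only NIKA+EMDR v NIKA, from pre-test | none |
| Maternal PCL-5 | none | mean change | none |
| Maternal BSI-18 | none | none | none |

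The power calculations state two-sided testing, so a mean shift in the harmful direction can be detected wherever the table says mean change. I assume the child outcomes are tested the same way.

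**3. Why a mean comparison does not replace a count.** Suppose 15% of treated mothers worsen by 1 SD and the mean change relative to waitlist is −0.6 SD. The other 85% then change by x, where 0.15 × 1 + 0.85x = −0.6. So x = −0.75/0.85 = −0.88 SD. The 15% is an assumption made for illustration.

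**4. What a by-arm table could deliver.** The article gives no worsening rates, so those below are assumptions. The 95% half-width for a risk difference is 1.96 × √[(p₁(1−p₁) + p₂(1−p₂))/n].
- 5% v 15%: p(1−p) sums to 0.0475 + 0.1275 = 0.175. At n = 75 the half-width is 9.5 points (difference 10, CI 0.5 to 19.5). At n = 40 it is 13.0 points (CI −3 to 23).
- 10% v 30%: the sum is 0.09 + 0.21 = 0.30. The half-width is 12.4 points at n = 75 and 17.0 at n = 40.
- Higher rates widen the intervals. For 20% v 40% the half-widths are 14.3 and 19.6 points.

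Power for 5% v 15% is 53% at 75 per arm and 32% at 40 per arm, so a test would not be informative.

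If no one in an arm worsened, the one-sided 95% upper bound is 1 − 0.05^(1/n): 3.9% for n = 75 and 7.2% for n = 40.

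**5. The missing phase 1 comparison of PCL-5 and BSI-18.** The difference detectable with 80% power is (1.960 + 0.842) × √(2/75) = 0.46 SD, and the 95% half-width is 1.960 × √(2/75) = 0.32 SD. The same simple two-group assumptions apply.

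**The case against.** The strongest reply is that this is a journal article. A deterioration table with thresholds and intervals is ordinary content for a full protocol or analysis plan, and its absence alone would be no finding. I accept that. The point rests on what the harms section does say: it fills the item with an expectation and does not describe or point to a method.

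Several stronger readings are tempting, and the article does not support them.
- *That no comparison could reveal harm.* Average worsening would show in phase 2 PCL-5 and in phase 1 parenting and child outcomes.
- *That the trial cannot say whether anyone got worse.* The scales are collected throughout, and nothing prevents a count. The count is simply not planned.
- *That distress is ignored, or could only be seen in treated mothers.* At research appointments, which are alike in both arms, the researcher watches for distress, pauses if needed and points the mother to her social worker {18a}. Therapy sessions are supervised and checklists reviewed {11c}. Support received is coded from case files {12}. Only distress during intervention sessions is confined to treated dyads, and none of this is described as a harm comparison.
- *That the article contradicts itself.* Sample size {14} says the EMDR used here "is different from previous studies", and the rationale says its effectiveness "for the specific group of victimized parents after interparental violence has not yet been empirically investigated". Both statements concern effectiveness. The first explains a cautious effect size and refers to which memories are targeted, and the intervention section uses the standard Dutch EMDR protocol. They show that the evidence is indirect, not that the harm expectation is false.
- *That having no monitoring committee or interim look is an error.* Both are openly stated choices.

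It can also be said that the table would be too imprecise to settle safety. That is true, and it is why the table is proposed as description.

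**Conclusion.** The concern holds in a limited form. The harms section expects no harm because other studies reported none, and it describes no recording or by-arm comparison of harms. The planned analyses leave three gaps: individual worsening on any scale, BSI-18 in both phases, and maternal PCL-5 in phase 1. No planned estimate or primary conclusion is wrong as a result. This is a worthwhile, cheap improvement.

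The gain is modest: half-widths of about 10 to 12 points at 75 per arm and 13 to 17 at 40 per arm under the illustrative rates, and wider if worsening is common. Three assumptions apply. The planned arm sizes are reached. PCL-5 is taken at the pre-test, which follows from the description of similar appointments (the schedule figure is not shown). Individual change scores carry measurement noise, so only the difference between arms can be interpreted. The maternal scales capture symptom worsening, not every kind of adverse event, and the child scales omit infants under 12 months.

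**What to change.** - Replace the expectation in Adverse event reporting and harms {22} with a prespecified descriptive table. By randomised arm and phase, give the number and percentage of mothers whose PCL-5 or BSI-18 worsens beyond a threshold, with risk differences and 95% CIs.
- Do the same for child CATS and CBCL in children older than 12 months.
- The investigators set the thresholds and fix them before any by-arm data are examined. Mothers and staff know the allocation, so a moment of unblinding cannot serve as the marker.
- Add the phase 1 comparison of change in PCL-5 and BSI-18, NIKA versus waitlist.
- Tabulate by arm the professional support already coded from case files.
- State that the table is descriptive and that its intervals cannot rule out harm.

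The cost is one additional table and one additional phase 1 analysis of existing data. Sample size, design, treatments and instruments stay as they are.
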